### 12. ADVERSE EVENTS

### 12.1 Participant welfare and safety

There is no known health risk associated with any of the assessments or either IonaFFV or Iona SHAM CONTROL. The risk concerning participation in this study is believed to be low. Further, we anticipate that IonaFFV will reduce low mood or worry. In our experience from previous projects, participants are happy to participate and enjoy the assessment tasks. We will strive to use tasks that the participants experience as motivational and reinforcing whenever possible. This will also ensure a low attrition rate.

Because the trial is only focussed on people with mild to moderate depression or anxiety, the initial screening process will exclude anyone with a history of severe psychiatric disorder and those reporting elevated suicidality (PHQ-9>1). These individuals will be automatically guided towards appropriate information and sources of help. This process means that individuals likely to have significantly increased risk (e.g., for self-harm and suicidality), and/or for whom more intensive psychological and psychiatric treatment is appropriate, will not be included in the study.

Other than the intervention failing to produce an effect, there is nothing in the literature to suggest possible adverse effects of the assessments and interventions. As with all psychological interventions, individuals reflect on their difficulties, which can produce temporary increases in distress, but no more than would commonly occur in daily life. Versions of techniques within the intervention are commonly adopted within a general adult version of the Iona app previously employed as in an NHS Talking Therapies for anxiety and depression service and with no detected harmful effect. As such, the intervention within the trial may benefit individual participants. The likeliest outcome for users who do not find the intervention of benefit is their disengagement from it. In addition, all participants receive more intensive monitoring, with processes within IonaFFV and Iona SHAM CONTROL to identify and direct all relevant participants to potential sources of help.

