### 12.2 Risk management processes

As part of our policy for addressing risk and prioritising the welfare of participants there are 2 main processes in place.

The main indicators of harm will be completion of the PHQ-9 questionnaire by the participants in both study arms at all assessments (baseline, 6 weeks, 10 weeks). The PHQ-9 study questionnaire will be automatically screened by the AI function of the apps for signs of distress (defined as scores above 20 on PHQ-9 for depression or reports >1 on Question 9 of the PHQ-9). Outside of the research there is also a function within the apps to identify aspects of risk and through the SOS button, which if selected will automatically provide participants with recommended advice and signpost towards help (e.g. NHS and Armed Forces specific support services).

We will record all occasions where risk within IonaFFV or Iona SHAM CONTROL app has been highlighted and recorded and reported to the Trial Management Group and Sponsor to determine whether events are related to the treatments and to take appropriate action.

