### 12.3 Definitions

Standard definitions for Adverse Events etc are in Table 13 below. Because the current interventions are digital self-help rather than a medicinal product and involve no biological agent, it is not appropriate to define adverse events etc re any untoward medical occurrence – rather as a psychological intervention, appropriate adverse events would include those related to mental state and behaviour. Furthermore, given the study has no involvement from a mental health or community-based service it will not be possible to record Serious Adverse Events/Reactions or Suspected Unexpected Serious Adverse reactions, only Adverse Events (AEs) captured within the app, or Adverse Reactions (ARs) as determined by the Sponsor can be recorded.

1. Adverse Events (AE) may include significant worsening symptoms of anxiety, worsening symptoms of depression, as operationalized by a deterioration of movement from ‘mild or moderate’ (PHQ-9=>10); to ‘severe’ (PHQ-9=>20) levels of symptoms on the PHQ-9 at 6 weeks assessment or from 6 weeks assessment to 10 weeks assessment.
2. Adverse Reactions (AR) same as AE but where a relationship to the app can be determined.

The following definition is adapted to accommodate the status of the intervention as digital self-help (Table 13).

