**Table 13 Definitions of Events**

| **Term** | **Definition** |
| --- | --- |
| **Adverse Event (AE)** | Standard: Any untoward medical occurrence in a participant to whom a medicinal product has been administered, including occurrences which are not necessarily caused by or related to that product.  Adapted: Any deterioration in mental state or behaviour in a participant to whom the intervention has been administered, including occurrences which are not necessarily caused by or related to the intervention. |
| **Adverse Reaction (AR)** | Standard: An untoward and unintended response in a participant to an investigational medicinal product which is related to any dose administered to that participant.  The phrase "response to an investigational medicinal product" means that a causal relationship between a trial medication and an AE is at least a reasonable possibility, i.e., the relationship cannot be ruled out.  All cases judged by either the reporting medically qualified professional or the Sponsor as having a reasonable suspected causal relationship to the trial medication qualify as adverse reactions.  Adapted: An untoward and unintended response in a participant to an intervention which is related to any feature of the digital intervention administered to that participant.  The phrase "response to an intervention" means that a causal relationship between an intervention and an AE is at least a reasonable possibility, i.e. the relationship cannot be ruled out.  All cases judged by the Sponsor as having a reasonable suspected causal relationship to the intervention qualify as adverse reactions. |

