### 12.4 Recording and reporting of AEs and ARs

All AEs will be recorded within the app and reported to the Chief Investigator within 1 working day (24 working hours). If there is uncertainty that an AE event may reflect an AR, it will be reported to the Trial Steering Committee (TSC) and DMEC and if considered related to either of the apps, will be classified as an AR and reported to the trial Sponsor. who will escalate to the regulatory authority when considered appropriate.

In line with other complex intervention studies, we will monitor non-serious AEs and ARs that are not trial, or treatment related, serious deterioration, and active withdrawals from treatments. All occasions where the score on the PHQ-9 Q9 increases from 0/1 to 2/3 will be separately recorded. The reporting period for all events and reactions will be from first usage of the app until 10 weeks follow-up.

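### The PHQ-9 harm rules do not agree on start value, on the cut-off at 20, or on which system screens the questionnaire

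*Protocol*

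**What the plan says.** **Adverse event score rule.** Section 12.3 sets a worsening rule whose bands and cut-offs run "from ‘mild or moderate’ (PHQ-9=>10); to ‘severe’ (PHQ-9=>20) levels of symptoms on the PHQ-9". It is introduced as one example of what counts, not as a closed list: "Adverse Events (AE) may include significant worsening symptoms of anxiety, worsening symptoms of depression, as operationalized by a deterioration of movement". As to timing, the rule is applied "at 6 weeks assessment or from 6 weeks assessment to 10 weeks assessment".

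**Who is enrolled.** Table 8 admits PHQ-9 of 5 or more and below 20, and excludes 20 or more. Section 12.1 says "the trial is only focussed on people with mild to moderate depression or anxiety".

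**Wider definitions.** Table 13 defines an adverse event as "Any deterioration in mental state or behaviour in a participant to whom the intervention has been administered". Section 12.4 adds monitoring of "serious deterioration, and active withdrawals from treatments".

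**Automated triggers.** Section 12.2 has signs of distress "defined as scores above 20 on PHQ-9 for depression", or item 9 above 1. Section 13.1.2 logs each PHQ-9 above 20 that arises during use of either app, notifies the Lead Researcher and counts it as an adverse event, with no condition on the starting score. Section 13.5 shows a depression message at follow-up when the score is above 20.

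**Where scores are taken and screened.** Section 12.2 lists the PHQ-9 at baseline, 6 and 10 weeks as the main indicator of harm and has the apps' AI screen it. Section 12.4 says every adverse event is recorded in the app. Section 12.3 refers to "only Adverse Events (AEs) captured within the app", in a sentence explaining why serious events cannot be recorded. Section 8.8 places the baseline PHQ-9 in Qualtrics before randomisation, section 6.1 sends the app code only after randomisation, and sections 8.7 and 8.9 place the week 6 and week 10 measures in Qualtrics.

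**The concern.** The PHQ-9 carries most of the safety detection here. The apps have no human support, the team holds no GP details (13.1.2), and serious events are declared unrecordable (12.3). The rules built on this score should therefore give one answer for one score.

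They do not. The 12.3 label says mild or moderate, but its number starts at 10, while the trial enrols from 5. The same score of 20 is too severe for entry and severe in 12.3, yet it falls short of every automated trigger. And the system said to screen the questionnaire is not the one in which it is completed.

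At stake are consistent adverse event counts across the two arms, and a depression message for a woman who reaches the score that would have excluded her at the outset.

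**Working it through.** The plan gives no figure to reproduce. The check enumerates score values and sets the rules side by side.

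**Inputs**
- Entry scores: 5-19 (Table 8), which is 19 − 5 + 1 = 15 values.
- Severe scores: 20 or more (12.3). The PHQ-9 has nine items scored 0-3, so its maximum is 27, and 20-27 is 8 values.
- 12.3 rule: start at 10 or more, end at 20 or more.
- Trigger in 12.2, 13.1.2 and 13.5: above 20, that is 21-27, or 7 values.

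**Start value**
- Entry scores below 10: 5-9, 5 of 15 values.
- Week-6 scores below 20: 0-19, 20 values. Of these, 0-9 lie below the start: 10 of 20.
- A rise to 20 from entry 9 (20 − 9 = 11 points) or from entry 5 (20 − 5 = 15 points) is outside the 12.3 rule. A rise from 19 to 20 (1 point) is inside it.

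**Baseline to follow-up, all pairs ending severe: 15 × 8 = 120**

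| Start | End | Pairs | 12.3 rule | Above-20 trigger |
|---|---|---|---|---|
| 10-19 | 21-27 | 10 × 7 = 70 | met | met |
| 10-19 | 20 | 10 × 1 = 10 | met | not met |
| 5-9 | 21-27 | 5 × 7 = 35 | not met | met |
| 5-9 | 20 | 5 × 1 = 5 | not met | not met |

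**Week 6 to week 10, starts 0-19: 20 × 8 = 160 pairs.** In the same order: 70, 10, 10 × 7 = 70, and 10 × 1 = 10. Here 10 pairs meet neither rule.

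These are score combinations, not participants. The protocol gives no score distribution, so they cannot be turned into expected counts.

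**Reading the third row.** Whether those 35 pairs are adverse events by score depends on 13.1.2, which speaks of scores arising during app use. At the visits the PHQ-9 is completed in Qualtrics. Section 13.5 describes a message to the participant at that point, and the automated report to the Lead Researcher in section 13.4 concerns suicide risk. If 13.1.2 reaches visit scores, the 35 are covered by rule. If it does not, they rest on the general wording of Table 13. The text does not settle which.

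**Cut-off.** Exactly 20 is treated as severe in two places (Table 8 exclusion, 12.3) and as below threshold in three (12.2, 13.1.2, 13.5). One score value is affected.

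**Place of capture.** The baseline PHQ-9 comes before randomisation and the app code comes after it, so the app cannot screen the baseline score when it is given. The protocol describes no transfer of Qualtrics scores to the apps at weeks 6 and 10. By contrast, section 12.5 has researchers checking for events at end of treatment and follow-up, possibly prompted by the website; Table 9 schedules adverse event assessment at both visits; and sections 13.4 and 13.5 attach screens to the Qualtrics or follow-up website. The website route is the one the protocol works out, so the app wording is what needs correcting.

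**The case against.** The strongest case is that these are drafting slips with working safeguards around them. Section 12.3 says adverse events may include this worsening, so it is not a closed list. A rise from 5 to 20 is an adverse event under Table 13 on its face. Section 13.1.2 counts scores above 20 during app use whatever the start. The cut-off conflict touches one value on a 0-27 scale, and for starts of 10-19 that value is already an adverse event under 12.3, so only the signposting is lost. Section 13.1 also promises automatic feedback to participants indicating risk at follow-up. For place of capture, a website route exists.

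Most of this stands and limits the point. A reader might infer that women who enter at 5-9 and become severe go uncounted; 13.1.2 and Table 13 do not support that. A reader might also infer that a woman scoring 20 is left without help; she still has the in-app SOS button and, if item 9 is 2 or 3, the separate item 9 route. Nor do the documents show that visit-based harm goes unrecorded.

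What the objection does not remove is that the rules disagree. For a score of 20 from a start below 10, no score rule applies and the decision rests on general wording, whereas a 1-point rise from 19 is settled by rule. Reading the 10 in 12.3 as a slip for 5 would mend the entry range but still leave out week-6 scores 0-4.

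**Conclusion.** The inconsistency is real and modest in size: minor to should-fix.

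- **Start value.** The 12.3 rule does not match the enrolled range. The clear gap is exactly 20 from a start below 10: 5 of 120 pairs from entry, 10 of 160 from week 6. For 21-27 from those starts at the Qualtrics visits, coverage by score rule is unclear, not absent.
- **Cut-off.** A score of exactly 20 triggers no distress flag, no in-app adverse event log and no follow-up depression message, although it excludes at entry and is called severe.
- **Place of capture.** The app wording in 12.2 and 12.4 conflicts with collection in Qualtrics, and cannot be true of the baseline questionnaire.

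Undercounting of deterioration is a risk, not a shown result. The counts assume that the inequality signs are meant literally and that the apps receive no Qualtrics scores, since no transfer is described. The apps may hold a PHQ-9 of their own, but section 12.2 names the study questionnaire.

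**What to change.** - In 12.2, 13.1.2 and 13.5, change the total-score threshold from above 20 to 20 or more.
- In 12.3, keep 20 or more as the end point and apply the rule from any score below 20 at baseline or at week 6.
- In 12.2 and 12.4, name Qualtrics as the screener of the study PHQ-9 and as the source of visit-based adverse events in both arms, with in-app alerts logged separately. Align the passing reference in 12.3.

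A rise from 19 to 20 remains an adverse event, as under any threshold-crossing rule; the change is that larger rises to the same score are counted too.

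The cost is wording and an alert threshold on data already collected. A few more adverse events may be recorded; the number cannot be derived from the protocol.

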### 8.9 Trial assessments

Assessment will take place at baseline and then at 6 weeks post treatment start (equating to end of treatment) and 10-weeks post baseline representing the study endpoint. At both of these timepoints the participant will receive a request to complete the outcome measures with a URL included to take them to the UNIEXE Qualtrics page. The results of the assessments are only to collect research data for the trial and will not be provided to anyone outside of the study. The only exception to that would be if a participant indicates suicide risk and asks us to provide their assessment results to their medical practitioner. They would need to give written consent for this and provide us with the contact details to do so.

At the end of treatment, all participants will be asked to complete the MAUQ

to determine the acceptability and usability of the app.

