### 8.12 Withdrawal criteria

At any time, participants can choose whether they want to stop using the IonaFFV or Iona SHAM CONTROL intervention, or if they want to withdraw from the trial completely (including all assessments). A log will be kept of the participant number and date of all withdrawals from the trial. Participants who met the inclusion criteria at baseline will not be replaced. Participants that did not meet the criteria at baseline can be replaced and their data removed from the data set. Participants who withdraw from the trial will not be followed up. Once a participant withdraws from the study, they will still be able to use the app until the end of the study period if they choose.

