### 11.3 Statistical analysis plan

A detailed statistical analysis plan (SAP) is to be produced; the main points of the statistical analysis are summarised here. All participants will be included in each analysis, separated by arm. Missing data will be reported descriptively. No imputation will be performed due to the feasibility nature of the study, but patterns of missingness will be explored to inform future trial design.

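### The PHQ-9 deterioration rule in 12.3 has no baseline-to-week-10 comparison, so worsening first seen at week 10 counts only if week 6 was returned and scored 10 to 19

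*Protocol*

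**What the plan says.** Section 12.3 opens its list with "Adverse Events (AE) may include significant worsening symptoms of anxiety" and then gives the protocol's one operational rule for depressive worsening: "a deterioration of movement from ‘mild or moderate’ (PHQ-9=>10); to ‘severe’ (PHQ-9=>20) levels of symptoms", judged "on the PHQ-9 at 6 weeks assessment or from 6 weeks assessment to 10 weeks assessment". The start of the first limb is not written out, but only baseline can be meant.

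Four other provisions bear on whether the rule can be applied at week 10:

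- Section 12.2 makes the PHQ-9 the main indicator of harm "at all assessments (baseline, 6 weeks, 10 weeks".
- Section 12.4 sets the safety window: "The reporting period for all events and reactions will be from first usage of the app until 10 weeks follow-up".
- Section 8.9 sends separate requests at weeks 6 and 10: "At both of these timepoints the participant will receive a request to complete the outcome measures".
- Section 8.12 ends follow-up for withdrawal only: "Participants who withdraw from the trial will not be followed up". A missed form is not listed as withdrawal, and 10.7 tabulates week-6 and week-10 completion separately.

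On missing scores, 11.3 states: "No imputation will be performed due to the feasibility nature of the study".

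Other sections define or trigger adverse events differently. Table 13 counts a worsening of mental state or behaviour of any size, with no time window. Section 11.8 uses a rise of PHQ-9 item 9 to 2 or 3. Sections 12.2 and 13.1.2 use a total score above 20 or an item 9 score above 1, and 13.1.2 ties this to use of either app.

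**The concern.** A rule meant to cover harm up to week 10 should be able to use a week-10 score by itself. This one cannot. Take two women with a baseline of 14 and a week-10 score of 23. If the first scored 14 at week 6, she meets 12.3. If the second did not return the week-6 form, she does not. The same worsening from baseline is classified differently because of an intermediate form. A woman who improved to 8 at week 6 and then reached 23 is also missed, because the second limb needs a starting score of at least 10.

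What is at stake is the consistency of the deterioration count at the last safety assessment. The trial is small and few such events would be expected, so one misclassified woman is visible in the count.

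**Working it through.** The plan states no figure on this point, so there is nothing to reproduce. The check is to code the rule as written and apply it to every admissible score.

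**Inputs**
- Baseline PHQ-9 of those randomised: 5 to 19 (Table 8), which is 15 values. Ten of these, 10 to 19, satisfy the rule's starting condition.
- Severe score: 20 to 27, since nine items are scored 0 to 3 (Table 11), which is 8 values.
- Rule in 12.3: an event if (baseline 10–19 and week 6 ≥ 20) or (week 6 10–19 and week 10 ≥ 20).

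**Week 6 missing, week 10 severe**
- All baselines: 15 × 8 = 120 score pairs. The rule counts 0.
- Baseline 10–19: 10 × 8 = 80 pairs. The rule counts 0, including a move from 10 to 27.

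**Week 6 present and below 20, week 10 severe**
- Week 6 of 10–19: 15 × 10 × 8 = 1,200 combinations. The rule counts all 1,200.
- Week 6 of 0–9: 15 × 10 × 8 = 1,200 combinations. The rule counts 0.

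**Adding a baseline-to-week-10 limb at the same thresholds**
- Week 6 missing: 80 of the 120 pairs count, which is 80 of 80 with baseline 10–19. The other 5 × 8 = 40 have a baseline of 5–9, below the rule's own starting value.
- Week 6 of 0–9 with baseline 10–19: all 10 × 10 × 8 = 800 combinations count.

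**Would the above-20 trigger close the gap?** If it applies to the week-10 score, seven values qualify (21 to 27). It flags 10 × 7 = 70 of the 80 pairs, or 15 × 7 = 105 of all 120. A score of exactly 20 is severe under 12.3 but does not fire this trigger.

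These are counts of possible scores, not event rates.

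**Size.** The protocol gives no rate of week-6 non-completion. Suppose a fraction m of women who move from 10–19 at baseline to severe at week 10 missed week 6 at random. Then at least m of those moves go uncounted under 12.3; women who dip below 10 at week 6 add to that. This restates the assumption and is not an estimate. As an illustration, assume that all 30 women in an arm start at 10 or more and that 5% to 10% are severe at week 10: 30 × 0.05 = 1.5 to 30 × 0.10 = 3 women. With m assumed between 10% and 30%, the number missed through non-return is 1.5 × 0.10 = 0.15 to 3 × 0.30 = 0.9 of a woman per arm.

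**The case against.** The strongest reply is that 12.3 is not the only route to an adverse event. Its list is expressly open. Table 13 would cover a move from 14 to 23 whatever happened at week 6. Section 12.5 has researchers check for events at treatment end and at follow-up, 12.4 monitors serious deterioration, and 12.2 says the study PHQ-9 is screened for scores above 20.

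That reply stands against a stronger reading. A reader might infer that a woman who misses week 6 can never be recorded as an adverse event at week 10, or that the trial's whole adverse-event count is biased downward. The protocol supports neither, because it does not say the count is built from 12.3 alone.

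The reply does not remove the gap in 12.3:

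- Table 13 and the 12.5 check give no countable threshold, so two people could classify one record differently.
- The trigger in 12.2 and 13.1.2 uses a different cut-off, and 13.1.2 ties it to app use, while 8.9 collects week-10 measures on Qualtrics. Whether it reaches that form is unclear.
- The item-9 rules detect suicidal thoughts, not general worsening.
- Section 13.5 describes only an automated message for a high follow-up score.

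A reader might also infer that the arm returning fewer week-6 forms would look safer by some definite amount. The documents do not support this. They give no completion rates by arm, the sham app is designed to match usage (9.2), reminders go to everyone (8.7), and sections 11.5 to 11.7 list no between-arm comparison of deterioration counts. Week-6 events also enter the count, so a ratio worked out for week 10 alone would not describe the total.

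Finally, the no-imputation statement carries little weight, since imputation would not normally establish an individual event. It confirms only that nothing will fill the missing week-6 score.

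**Conclusion.** The gap is real but narrow. Under the operational rule in 12.3, a woman with a baseline of 10 to 19 and a severe week-10 score cannot be counted if week 6 is missing (0 of 80 score pairs) or below 10 (0 of 800 combinations). This follows from the wording and needs no assumption beyond baseline being the start of the first limb. It sits badly with 12.2 and 12.4, which carry the PHQ-9 as a harm indicator through week 10.

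The size of any undercount is unknown. On the assumptions shown, non-return of week 6 would cost less than one woman per arm. The conclusion concerns what 12.3 counts. Other sections may still record the same woman, but by criteria that do not match and need reconciling.

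**What to change.** Reword 12.3 so that worsening is judged from baseline at each of week 6 and week 10, at the thresholds the protocol already uses, and keep the week-6-to-week-10 comparison as an additional limb. Every randomised woman has a baseline PHQ-9 below 20, so the new comparison can be made whenever a week-10 score exists.

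In the same edit, reconcile 12.3 with Table 13, 11.8, 12.2 and 13.1.2. State which definition generates the reported deterioration count, whether a score of exactly 20 belongs in each rule, and whether the in-app trigger applies to the week-10 Qualtrics form. Women starting at 5 to 9 remain outside the 12.3 starting value even after this change. The text labels that starting level mild or moderate, so the intended coverage should be stated.

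The cost is one phrase in 12.3, one extra comparison on scores already collected, and the cross-references. No new data are needed.
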